#### Heel lift (intervention group)

Participants allocated to the intervention group will be given a pair of commercially available heel lifts (Clearly Adjustable) for bilateral use. The heel lifts are 12 mm in height and made from firm (Shore A 90) multi-layered clear vinyl. To maximise comfort, a 3.2-mm PPT Ultralux top cover will be adhered to the top surface (Fig. 2). The heel lifts will be reduced in 1-mm increments if required (e.g. heel slippage) and the final height will be recorded at baseline. Small, medium and large heel lifts will be available and issued according to the participant’s shoe size. Participants will be shown how to use the heel lifts and asked to wear them for at least 8 h every day. The decision to use these heel lifts were based on the findings of a previous trial that reported this intervention to be safe and more effective for some clinical outcomes than eccentric calf exercises for mid-portion AT over 12 weeks [14].

**Fig. 2 Fig2:**
[figure not shown]
Interventions. **a** Lateral view of heel lift. **b** Lateral view of sham heel lift. **c** Dorsal view of interventions (top: heel lift and bottom: sham heel lift)

#### Sham intervention (control group)

Participants allocated to the control group will receive a pair of the sham heel lifts. The following sham intervention may be used; however, we will pilot other interventions (i.e. made of different materials and dimensions) prior to the trial and reserve the right to change the design if required (this will be reported as a change in the protocol on the website trial registration). The intended design of the sham intervention is to not plantarflex the ankle joint but appear as identical to the heel lifts as possible. To achieve this, the sham heel lift will extend the entire length of the shoe and will be made of the same materials as the heel lift (i.e. 1 mm of clear vinyl with a 3.2-mm PPT Ultralux top cover) (Fig. 2). This sham heel lift is necessary in this trial due to participant’s expectation of receiving a ‘take-home’ intervention (i.e. minimises resentful demoralization [30]). The sham intervention will be sized according to shoe size and trimmed (if needed) to fit into the participant’s footwear. Participants will be shown how to use the sham intervention and asked to wear them for at least 8 h every day.

#### Education

Participants will be given education regarding the amount of acceptable pain during activity, based on the pain-monitoring model [31]. This approach allows individuals with Achilles tendinopathy to continue with some level of physical activity, while being safe and produces comparable outcomes to complete rest from aggravating activities [31]. Participants will be asked to maintain their regular activities/occupations (rather than complete rest) after receiving their allocated ‘shoe insert’, provided the amount of pain they experience in the Achilles tendon pain does not exceed a score of 5 on a 0–10 pain scale, where 0 is no pain and 10 is worst pain imaginable during exercise/activity. The pain after usual physical activities can reach a 5 on the pain scale but should subside by the following morning. During activity, if the pain in the Achilles tendon exceeds 5 on the pain scale, participants will need to reduce their activity/exercise (if possible).

During the trial, participants will be asked to refrain from using any other treatments for their Achilles tendon pain (besides what they are given in this trial). They will be able to take 500 mg of paracetamol on an ad hoc basis if the tendon(s) is painful and asked to document usage. If participants experience any adverse event (e.g. develop new pain) or have concerns (e.g. uncertainty on using their allocated intervention), they will be encouraged to contact a trial investigator (JB, with support from SM and PM), who will decide if it is safe for the participant to continue with their allocated intervention.

### Treatment credibility/expectation

The outcome may be influenced by the participant’s expectations and their beliefs about the credibility of the intervention [32, 33]. Therefore, the credibility of the intervention (participants’ beliefs about the logic underpinning the intervention) and expectancy (participants’ perceptions of how much they may benefit) will be quantified using the Credibility/Expectancy Questionnaire (CEQ) [34]. The CEQ will be administered after the random allocation of the interventions. The CEQ consists of six items that ask participants to rate the credibility of the intervention and their expectancy on a 9-point Likert scale. Higher scores on the scale indicate that the participant considers the intervention to be credible and expects it to be effective. The CEQ is a reliable scale, shown to have good internal consistency and test–retest reliability [34].

### Outcomes

Primary and secondary outcome measures [35] will be collected at baseline and at 12 weeks (the endpoint). A summary of the data collection time points for each of the outcome measures is shown in Fig. 3. Follow-up data will be collected using REDCap™ surveys; however, participants will have the option of a postal survey. Where participants have bilateral symptoms, they will be asked to report for their most painful side (or right side, if the Achilles tendons are equally painful) to maintain independence of data [36, 37].

**Fig. 3 Fig3:**
[figure not shown]
SPIRIT diagram of enrolment, interventions and assessments for the LIFT trial

#### Primary outcome

The primary outcome will be pain intensity at its worst in the previous week using a 11-point numerical rating scale (NRS) with terminal descriptors of ‘no pain’ (score = 0) and ‘worst pain possible’ (score = 10) [38]. This outcome was chosen as it is a core domain in the consensus statement for tendinopathy [35].

#### Secondary outcomes

The following secondary outcomes will be measured:Pain and disability (measured using the Victorian Institute of Sport Assessment—Achilles (VISA-A)) [39].Global Rating of Change Scale (measured using a 15-point Likert scale ranging from a ‘very great deal worse’ to a ‘very great deal better’). This variable will be dichotomized, with ‘effective’ defined as “somewhat better” or above [40];Function (measured using the Lower Extremity Functional Scale (LEFS) [41]);Health-related quality of life (measured using the VAS component of the EuroQol 5 Dimension 5 Level (EQ-5D-5L) questionnaire [42]);Level of physical activity (measured using the International Physical Activity Questionnaire—short form (IPAQ-SF) [43]).

#### Other outcomes

##### Co-interventions

The use of co-interventions to relieve pain at the Achilles tendon will be measured at 4, 8 and 12 weeks via a REDCap survey™. The use of paracetamol rescue medication (number of participants and mean consumption) or any other treatment (e.g. exercise) to manage their Achilles tendon pain.

##### Adverse events

Adverse events from the interventions (such as skin blistering or the occurrence of new pain or injuries in other areas of the foot and body) will be assessed at 4, 8 and 12 weeks via a REDCap survey™. Participants will be asked to document the type of adverse event, the body location, the duration and severity of the event [44]. An open-response type format will also be available for participant responses.

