### Data monitoring

Data will be accessible to the trial investigators (JB, SM, AG, ST, PM) and will be stored on a password-protected computer (JB) and uploaded to LabArchives, a secure cloud-based server. This study will have a Trial Management Committee that will be comprised of study investigators (JB, SM, AG, ST, PM). The Committee will meet every 4 weeks to review safety reports, data quality, protocol adherence and retention rates. An independent Data Monitoring and Ethics Committee was considered to not be needed for this trial, as it is relatively short and includes two safe and common interventions [14]. In addition, the participants are not considered to be vulnerable [59, 60]. There will be no formal interim analysis.

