### Statistical analysis

Statistical analysis will be performed using the most recent version of SPSS (IBM Corp., Armonk, NY, USA) available at the time of analysis. Data will be double entered to minimise errors. Demographic data and anthropometric characteristics (e.g. gender, age, foot posture using the FPI, etc.) will be reported by the treatment arm.

The intention-to-treat principle will be used for all participants [61]. Multiple imputation will be used to replace missing data for the primary and secondary outcome measures [62], with the exception being ‘Global Rating of Change Scale, where no data substitution will be applied. Standard tests to assess continuous data for normal distribution will be used and transformation performed if required. The primary outcome measure assessed will be pain intensity (at its worst) at 12 weeks. Continuously scored outcome measures (pain intensity (NRS-11), VISA-A, LEFS, EuroQol 5—VAS, IPAQ-SF and biomechanical outcomes) will be analysed using an ANCOVA with adjustment for baseline scores [63].

Dichotomous data (Global Rating of Change Scale, adverse events and use of co-interventions) will be compared using relative risk, absolute risk increase and number needed to treat or harm. Intervention adherence and CEQ data will be compared between groups using independent *t*-tests. To complement point estimates, standard deviations, 95% confidence intervals and *p*-values will be calculated where appropriate.

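### The adverse-event survey is scoped to events caused by the inserts, so the harm comparison is filtered by perceived cause and worsening of the treated tendon is not prompted for

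*Protocol article*

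**What the plan says.** The Adverse events section of the protocol article sets the scope of the survey at weeks 4, 8 and 12: "Adverse events from the interventions (such as skin blistering or the occurrence of new pain or injuries in other areas of the foot and body"). It then lists what is recorded: "Participants will be asked to document the type of adverse event, the body location, the duration and severity of the event". It adds that "An open-response type format will also be available for participant responses".

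The Education section describes a second route, in which participants contact a trial investigator, and gives it a wider scope: "If participants experience any adverse event (e.g. develop new pain) or have concerns".

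The Statistical analysis section takes adverse events into a between-arm comparison: "Dichotomous data (Global Rating of Change Scale, adverse events and use of co-interventions) will be compared using relative risk", together with absolute risk increase and number needed to treat or harm. It does not say whether those events come from the survey alone or also from contacts with an investigator.

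**The concern.** Randomisation already deals with causality in a comparison of harms. If every event is counted, whatever its presumed cause, a difference between arms beyond chance can be put down to allocation. If events are first filtered by whether someone blames the device, the comparison mixes how often events occur with how readily each device is blamed. The participant, who completes the survey, is poorly placed to make that judgement, having been told only that two types of shoe insert are being compared.

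The treated tendon matters here because a change in Achilles tendon load is the proposed mechanism of the heel lift (Background and rationale; Biomechanical assessment). It is therefore an obvious site for harm. A participant guided by the survey's examples would think first of skin problems and of new pain elsewhere, and might not think of a worsening of the pain that brought them into the trial.

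**Working it through.** No figure in the protocol depends on this point. Its one computed design figure, the sample size, rests on the pain score. The check is therefore a reading of the text, with one line of algebra.

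**1. Which words set the scope.** In the Adverse events section, the restriction to events arising from the interventions stands before the words that introduce examples. It is the scope. The skin, new-pain and other-area items come after those words and are illustrations.

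**2. Who applies the scope.** The survey is completed by the participant in REDCap. The article gives no later step in which someone else assigns cause. Read as written, attribution is settled when the participant decides whether to enter an event.

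**3. What the filter does to the comparison.** Let *p* be the true event probability, the same in both arms. Let *a*(L) and *a*(S) be the probabilities that an event is attributed to the lift or to the sham, and so recorded.

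- Recorded risk: *p* × *a*(L) in the lift arm and *p* × *a*(S) in the sham arm.
- Recorded relative risk: [*p* × *a*(L)] / [*p* × *a*(S)] = *a*(L) / *a*(S).
- Recorded risk difference: *p* × [*a*(L) − *a*(S)].

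With no true difference, the recorded relative risk equals 1 only if attribution is the same in both arms. The protocol gives none of *p*, *a*(L) or *a*(S), so no numerical bias can be derived.

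**4. Could attribution differ?** The Interventions section describes a firm 12 mm heel lift, which may be reduced in 1 mm steps, and a full-length sham with 1 mm of vinyl. Both carry a 3.2 mm top cover. The devices differ in height and form. Limited disclosure hides the hypothesis but not how the insert feels. A difference in attribution is possible, and the text does not show which way it would go.

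**5. Would the other data pick up a tendon event?**

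| Source | What it covers | What it can miss |
|---|---|---|
| Primary outcome | "The primary outcome will be pain intensity at its worst in the previous week using a 11-point numerical rating scale (NRS") | Anything resolved before the final week |
| Timing of outcomes | "Primary and secondary outcome measures [35] will be collected at baseline and at 12 weeks (the endpoint") | Weeks 4 and 8 |
| Global Rating of Change | Dichotomised at somewhat better or above | Worse is merged with unchanged |
| Co-interventions | Treatment used for Achilles pain, at weeks 4, 8 and 12 | A flare that was not treated; participants are asked to avoid other treatment apart from paracetamol |
| Contact with an investigator | Any adverse event or concern | Depends on the participant making contact; not stated to join the analysed events |

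An untreated flare that settles before the last week and is not raised with an investigator has no dedicated place in these data.

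**The case against.** A reader might infer something stronger: that events in the treated tendon are excluded from the survey, and so are left out of the harm comparison and of the regular safety review. The documents do not support that. The reference to other body areas is an example and not a limit. The body-location and open-response fields can hold an Achilles event. The route to an investigator is not restricted by site or cause. The committee's remit is equally open: "The Committee will meet every 4 weeks to review safety reports, data quality, protocol adherence and retention rates". Nothing confines those safety reports to survey entries.

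Three further objections deserve weight.

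- Treating worsening of the index condition as efficacy and new events elsewhere as harm is a common structure. Tendon pain is compared between arms at week 12, and treatment for Achilles pain is also compared. This stands for lasting or treated worsening, but not for an untreated flare that resolves.
- The wording comes from an article that condenses a fuller protocol, and the survey form is not shown. The form may ask more broadly. This limits how firmly the point can be put. It does not remove it, because the article states a scope, and that scope differs from the one in its own Education section.
- Unequal attribution is conjecture: the sham is designed to look as similar as possible, and equal attribution leaves the relative risk undistorted when there is no true difference. This also stands, which is why no size is claimed.

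**Conclusion.** The point holds as a cheap improvement. As written, the survey counts that feed the relative risk and number needed to harm are filtered by perceived cause. Participants are also not prompted to report worsening or injury of the treated tendon, and two sections give adverse events different scopes. The possible distortion equals the ratio of attribution probabilities in the two arms; neither its size nor its direction can be taken from the documents.

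The conclusion assumes that the survey item follows the article's wording and that the participant applies it. If the form already asks for all events regardless of cause, only the article's sentence needs correcting.

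**What to change.** Word the existing week 4, 8 and 12 item along these lines: any new or worsened symptom or injury at any site, including either Achilles tendon, whether or not you think it is due to the shoe insert. A follow-up question can ask whether the participant attributes it to the insert.

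In the Statistical analysis section, state that the between-arm relative risk, absolute risk increase and number needed to harm use all such events, including those reported directly to an investigator, and that attributed events are reported as a subset. Align the Adverse events and Education sections to the same definition.

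The cost is the rewording of one survey item and a few sentences of text, with no extra visit. The downside is more background events in both arms, and so a slightly noisier comparison.

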##### Adherence

Adherence will be measured at 4, 8 and 12 weeks via a REDCap survey™. Participants will be asked to provide information regarding the average number of hours per day and number of days they have worn the heel lifts during the preceding 4 weeks.

### Biomechanical assessment

At baseline, a subpopulation of participants who volunteer (*n* = 40) will undergo a biomechanical assessment to evaluate the acute changes in the biomechanical function of the Achilles tendon as this is the proposed mechanism of action of heel lifts. The variables of interest are Achilles tendon load (ATL), ankle joint moments and plantar/dorsiflexion range of motion (ROM), stance phase duration (SPD), ground reaction force (GRF) and tibial acceleration. One researcher (JB) will perform the assessment, with the support of experts in biomechanical analysis (ST, AG).

After completing a standardised and progressive 7-min warm-up, participants will be asked to walk (5 min) and run (3.5 min) with and without their allocated intervention (i.e. heel lift or sham heel lift) in four testing conditions: (i) walking, shoe only; (ii) walking with the allocated intervention; (iii) running, shoe only and (iv) running with the allocated intervention. The footwear used in testing will be standardised, using the same zero drop Merrell® shoe. The testing sequence will be randomised by a single author (JB). The gait conditions will be fixed at the participant’s optimal walking and preferred running speed to minimise the effect on biomechanical parameters [45].

Optimal walking speed (*V*) will be calculated to be a fourth of maximal walking speed, using the following calculation: *V* = sqrt(*L* × *g* × 0.25) [46]. The formula is based on the Froude number (0.25), leg length (*L*) and acceleration of gravity (*g*). Preferred running speed will be determined using a previously outlined method [47, 48]. Speed will be increased in increments of 0.1 km/h until they first report they have exceeded their preferred ‘comfortable’ running pace. Speed will then be decremented by 0.1 km/h until the participant has confirmed that their ‘comfortable’ running speed has been passed going down. This procedure will be repeated three times and speeds will be averaged to determine the preferred running speed. In between testing, participants will be given as long as required to recover and withdraw if pain exceeds 5 out of 10 on a VAS at any time during the trials [31].

#### Direct measurement of biomechanical variables

Participants will walk and run on an instrumented treadmill (Advanced Mechanical Technology Inc., Watertown, MA, USA) that collects GRF at a sampling rate of 1000 Hz. The grade of the contact surface of the treadmill will be maintained in a horizontal position (0%) throughout testing. Three-dimensional kinematic data will be recorded at a sampling rate of 200 Hz from a 14-camera VICON B-10 system (Oxford Metrics Ltd., Oxford, UK). A biomechanical model will be reconstructed from 38 retroreflective markers, placed on proper landmarks of body segments (Additional file 3), which our research team has used previously [49]. Two inertial measurement units (IMUs) will be placed and aligned with the left and right shank respectively to collect tibial acceleration data. Kinematic, IMU and ground reaction force data will be synchronised and collected through Nexus 2.15 software (Vicon Motion Systems Ltd., Oxford, UK).

#### Achilles tendon load—computed measurement

Achilles tendon load (ATL) will be determined using a method described in similar trials [50–52]. Achilles tendon forces will be estimated by dividing the ankle plantar flexion moment (PFM) by the Achilles tendon moment arm (MA). The MA will be calculated to 1° increments of ankle flexion (*θ*) using the following formula [53], which was derived from magnetic resonance imaging [54]: MA =  − 0.5910 + 0.08297 × *θ* − 0.0002606 × *θ*^2^. The PFM will be computed around the ankle flexion/extension axis (the axis connecting the medial and lateral malleoli) using Newton–Euler inverse dynamics approach and normalised to body mass (kg) [49].

### Sample size

The sample size has been determined a priori using G*Power [55] based on pain intensity at its worst in the previous week as the primary outcome measure. We calculated the sample size using an *f*-test, analysis of covariance (ANCOVA). Using an allocation ratio of 1:1, 90% power, minimal clinically important difference of 1.5 units out of 10 [56], standard deviation of 2.3 [14], moderate effect size [57] (*f* = 0.33) and a significance level set at *a* < 0.05, we estimate that a total of 108 participants will be required (99 and an extra 9 for 10% drop-out) [58].

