### Interventions

#### Randomisation and blinding

Participants will be randomised to one of two groups: an intervention group (heel lifts) or a control group (sham heel lifts). Both groups will also receive the same guideline recommended education about activity modification. Using Sealed Envelope (https://www.sealedenvelope.com/), participants will be randomised on a 1:1 ratio with random permuted block sizes. Participants will be blinded via limited disclosure, as they will be told that the study will be comparing two types of ‘shoe inserts’. Primary and secondary outcomes will be self-reported; thus, this trial will be assessor blinded. The clinician (JB) administering the interventions will be unable to be blinded. The instructions on using the shoe inserts and education provided will be detailed in a brochure provided to the participants at baseline (Supplementary Material).

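### The 9 participants added to 99 cover about 8% loss, not the stated 10%; a 10% loss from 108 leaves about 97, a minor shortfall against the 99 required

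*Protocol article*

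**What the plan says.** The Sample size section of the protocol article names the method ("We calculated the sample size using an *f*-test, analysis of covariance (ANCOVA") and gives these inputs:

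- Allocation and power: "Using an allocation ratio of 1:1, 90% power".
- Difference to detect: "minimal clinically important difference of 1.5 units out of 10" on the pain scale.
- Spread and effect size: "standard deviation of 2.3 [14], moderate effect size [57", with f given as 0.33.
- Significance: "a significance level set at *a* < 0.05".

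The section concludes: "we estimate that a total of 108 participants will be required (99 and an extra 9 for 10% drop-out".

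Under Statistical analysis, the continuous outcomes, including the primary one, "will be analysed using an ANCOVA with adjustment for baseline scores", so the planned analysis matches the method used for the sample size.

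**The concern.** The total, the evaluable number and the drop-out rate appear in one sentence, and the three cannot all be right. To allow for a loss of 10% of those randomised, the evaluable number is divided by 0.9. Adding a percentage of the evaluable number instead gives too few. Here even that shortcut would give 109, not 108.

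At stake is the accuracy of a headline planning figure. The 108 also stands in the Abstract and will be carried into the results paper. A reader who applies the stated 10% to 108 gets fewer evaluable participants than the plan says it needs for 90% power. The design, the analysis and the interpretation of the result are not at stake.

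**Working it through.** **Inputs.** From Sample size: difference 1.5, SD 2.3, f = 0.33, significance level 0.05, power 90%, 99 evaluable, 9 extra, 10% drop-out, 108 in total. From Statistical analysis: adjustment for baseline, taken as one covariate. Two groups.

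**Formula.** Power of the ANCOVA F-test comes from the noncentral F distribution with 1 and N − 3 degrees of freedom and noncentrality λ = f² × N.

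**Step 1: reproduce the 99.**

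- f = 0.33, N = 99: λ = 0.1089 × 99 = 10.78, power 90.2%.
- f = 0.33, N = 98: power 89.9%.

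So 99 is the smallest total that reaches 90% at f = 0.33. The plan's evaluable number reproduces exactly.

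**Step 2: check the drop-out allowance.**

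| Quantity | Arithmetic | Result |
|---|---|---|
| Extra as a share of those randomised | 9/108 | 8.3% |
| Extra as a share of the evaluable number | 9/99 | 9.1% |
| Total needed for 99 evaluable after 10% loss | 99/0.9 | 110 |
| Total if 10% of 99 is simply added | 99 × 1.10 = 108.9 | 109 |
| Evaluable after 10% loss from 108 | 108 × 0.9 = 97.2 | about 97 |

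No reading of 10% leads from 99 to 108. The correct total is two participants higher.

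**Step 3: power with 97 evaluable.**

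- At the stated f = 0.33: λ = 0.1089 × 97 = 10.56, power 89.6%. Against 90.2% at 99, the drop-out slip costs about 0.6 points and puts power about 0.4 points below the 90% target.
- At the unrounded f = 1.5/(2 × 2.3) = 0.3261: λ = 10.31, power 88.9%.

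**Step 4: how firm is the 88.9%?** It depends on two things the protocol does not settle.

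- *Rounding of the SD.* A printed 2.3 can stand for anything from 2.25 to 2.35. At 2.25, f = 1.5/4.5 = 0.333 and 97 evaluable give 90.1%. At 2.35, f = 1.5/4.7 = 0.319 and they give 87.5%.
- *Gain from the baseline covariate.* The protocol does not say whether 2.3 is a raw SD or one already adjusted for baseline. If it is raw and the baseline to week-12 correlation is r (assumed; the protocol gives none), the effective effect size is f/√(1 − r²). With f = 0.3261 and 97 evaluable, power is 88.9% at r = 0, 90.0% at r = 0.2, 91.5% at r = 0.3 and 95.6% at r = 0.5. If 2.3 is already a residual SD, there is no such gain.

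**The case against.** The strongest reply is that the slip is trivial. At the plan's own f, power after a true 10% loss is 89.6%, which is 90% to the nearest whole percent, and two participants separate 108 from 110. If 2.3 is a raw SD, a baseline correlation of about 0.2 already restores 90%, and the planned analysis does adjust for baseline. This stands as to size. It does not make 9 a 10% allowance. Nor can the point be put down to an article's brevity, since all four figures (99, 9, 10% and 108) are printed.

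Stronger readings are tempting, and the protocol does not support them:

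- *That f was inflated from 0.326 to 0.33.* This is ordinary two-decimal rounding, and f = 0.33 is stated openly. The SD is itself rounded, and an SD of 2.27 gives f = 1.5/4.54 = 0.330.
- *That a larger evaluable number, and so a larger total than 110, is required.* That would follow only if 2.3 were exact.
- *That an odd 99 conflicts with equal allocation.* The section on randomisation says "participants will be randomised on a 1:1 ratio with random permuted block sizes". The 99 is an intermediate evaluable count, and the 108 randomised splits into 54 and 54.
- *That the trial fails to reach 90% power.* Whether it does after 10% loss depends on the unrounded SD and on whether 2.3 is raw or residual, neither of which is given.

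**Conclusion.** The drop-out statement is wrong as written: 9 extra participants cover 8.3% loss, and a 10% loss from 108 leaves about 97 against the required 99. This rests only on figures printed in one sentence and needs no assumption.

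The consequence is minor. Power after 10% loss is 89.6% at the stated f = 0.33, against 90.2% with 99. The lower figure of 88.9% assumes an SD of exactly 2.3 and no benefit from baseline adjustment. The 99 itself and the choice of f are sound. This is a correction to wording, not evidence that the trial is too small.

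**What to change.** Keep 108 randomised and make the sentence agree with itself in one of two ways:

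1. Restate the allowance: 108 randomised allows for about 8% loss, leaving 99 evaluable and 90% power at f = 0.33.
2. Keep the 10% drop-out and restate what follows from it: about 97 evaluable, with about 89% to 90% power for a difference of 1.5 points and an SD of 2.3.

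Either is a change of one sentence, to be carried into the results paper. No participant is added and nothing in the design or analysis changes. The only cost of the second option is a stated power up to about one point lower; the first lowers the stated drop-out allowance from 10% to about 8%.
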